### **Ethics and dissemination**

The two relevant ethical committees, “*Comitato Etico Pavia*” and “*Comitato Etico di Brescia*”, have approved this protocol, respectively on September 5, 2018 and on May 7, 2019.

All patients or caregivers sign the informed consent prior to study enrolment and randomization.

Once completed the list of SIs, the PIs will communicate their names and affiliations to the Ethical Committees. It may happen during the conduction of telephone interviews, that patients demonstrate a potentially hazardous comprehension deficit of the prescribed therapies, e.g. a patient who ignores or refuses the prescription of parenteral or oral anticoagulants. In such cases, the interviewing PIs will promptly address the patients to his/her GP or send him/her back to the emergency department.

## Dissemination policy

Patient's data will not be shared with third parties and will always be used respecting their privacy. At the end of the study, PI's will produce a scientific paper for submission to peer-reviewed journals in the field of general medicine or emergency medicine.

In case of publication, PIs will participate as authors of the paper, whereas all participating SIs will result as contributors.

Manuscript preparation will follow the CONSORT guideline: <http://www.equator-network.org/resource-centre/library-of-health-research-reporting/reporting-guidelines/>. The authors of the publications will be decided on the basis of indications contained in the Uniform Requirements for Manuscripts ([http://www.icmje.org/urm\\_full.pdf](http://www.icmje.org/urm_full.pdf)).

## Funding

This study is not sponsored.

The conduction of the study does not add additional costs for the participating institutions.

The interventional videos are freely available on several websites and are not covered by copyright or royalties. Phone calls are made from a telephone within the IRCCS Ospedale San Matteo at negligible costs.

The software used for phone calls management is also freely downloadable from the internet.

Since the intervention under study is an educational video and not a drug, we will not stipulate any insurance, as the intervention does not constitute a potential harm for patients.

## CONSORT 2010 checklist of information to include when reporting a randomised trial\*

| Section/Topic             | Item No | Checklist item                                                                                                                        | Reported on page No |
|---------------------------|---------|---------------------------------------------------------------------------------------------------------------------------------------|---------------------|
| Title and abstract |         |                                                                                                                                       |                     |
|                           | 1a      | Identification as a randomised trial in the title                                                                                     | 1                   |
|                           | 1b      | Structured summary of trial design, methods, results, and conclusions (for specific guidance see CONSORT for abstracts)               | 2-4                 |
| Introduction       |         |                                                                                                                                       |                     |
| Background and objectives | 2a      | Scientific background and explanation of rationale                                                                                    | 4                   |
|                           | 2b      | Specific objectives or hypotheses                                                                                                     | 4                   |
| Methods            |         |                                                                                                                                       |                     |
| Trial design              | 3a      | Description of trial design (such as parallel, factorial) including allocation ratio                                                  | 5                   |
|                           | 3b      | Important changes to methods after trial commencement (such as eligibility criteria), with reasons                                    | NA                  |
| Participants              | 4a      | Eligibility criteria for participants                                                                                                 | 5                   |
|                           | 4b      | Settings and locations where the data were collected                                                                                  | 5                   |
| Interventions             | 5       | The interventions for each group with sufficient details to allow replication, including how and when they were actually administered | 5-6                 |
| Outcomes                  | 6a      | Completely defined pre-specified primary and secondary outcome measures, including how and when they were assessed                    | 6-7                 |
|                           | 6b      | Any changes to trial outcomes after the trial commenced, with reasons                                                                 | 7                   |
| Sample size               | 7a      | How sample size was determined                                                                                                        | 7                   |
|                           | 7b      | When applicable, explanation of any interim analyses and stopping guidelines                                                          | NA                  |
| Randomisation:     |         |                                                                                                                                       |                     |
| Sequence generation       | 8a      | Method used to generate the random allocation sequence                                                                                | 7                   |
|                           | 8b      | Type of randomisation; details of any restriction (such as blocking and block size)                                                   | 7                   |
| Allocation                | 9       | Mechanism used to implement the random allocation sequence (such as sequentially numbered containers),                                | 7                   |

|                                                      |     |                                                                                                                                                   |                    |
|------------------------------------------------------|-----|---------------------------------------------------------------------------------------------------------------------------------------------------|--------------------|
| concealment mechanism                                |     | describing any steps taken to conceal the sequence until interventions were assigned                                                              |                    |
| Implementation                                       | 10  | Who generated the random allocation sequence, who enrolled participants, and who assigned participants to interventions                           | 7                  |
| Blinding                                             | 11a | If done, who was blinded after assignment to interventions (for example, participants, care providers, those assessing outcomes) and how          | 7                  |
|                                                      | 11b | If relevant, description of the similarity of interventions                                                                                       | NA                 |
| Statistical methods                                  | 12a | Statistical methods used to compare groups for primary and secondary outcomes                                                                     | 8                  |
|                                                      | 12b | Methods for additional analyses, such as subgroup analyses and adjusted analyses                                                                  | 8                  |
| Results                                       |     |                                                                                                                                                   |                    |
| Participant flow (a diagram is strongly recommended) | 13a | For each group, the numbers of participants who were randomly assigned, received intended treatment, and were analysed for the primary outcome    | 8-9; 15-16         |
|                                                      | 13b | For each group, losses and exclusions after randomisation, together with reasons                                                                  | 8-9; 15-16         |
| Recruitment                                          | 14a | Dates defining the periods of recruitment and follow-up                                                                                           | 8                  |
|                                                      | 14b | Why the trial ended or was stopped                                                                                                                | NA                 |
| Baseline data                                        | 15  | A table showing baseline demographic and clinical characteristics for each group                                                                  | 12-13              |
| Numbers analysed                                     | 16  | For each group, number of participants (denominator) included in each analysis and whether the analysis was by original assigned groups           | 9                  |
| Outcomes and estimation                              | 17a | For each primary and secondary outcome, results for each group, and the estimated effect size and its precision (such as 95% confidence interval) | 9-10               |
|                                                      | 17b | For binary outcomes, presentation of both absolute and relative effect sizes is recommended                                                       | 9-10               |
| Ancillary analyses                                   | 18  | Results of any other analyses performed, including subgroup analyses and adjusted analyses, distinguishing pre-specified from exploratory         | Supplementary file |
| Harms                                                | 19  | All important harms or unintended effects in each group (for specific guidance see CONSORT for harms)                                             | NA                 |
| Discussion                                    |     |                                                                                                                                                   |                    |
| Limitations                                          | 20  | Trial limitations, addressing sources of potential bias, imprecision, and, if relevant, multiplicity of analyses                                  | 10-11              |
| Generalisability                                     | 21  | Generalisability (external validity, applicability) of the trial findings                                                                         | 10-11              |
| Interpretation                                       | 22  | Interpretation consistent with results, balancing benefits and harms, and considering other relevant evidence                                     | 10-11              |
| Other information                             |     |                                                                                                                                                   |                    |
| Registration                                         | 23  | Registration number and name of trial registry                                                                                                    | 3                  |
| Protocol                                             | 24  | Where the full trial protocol can be accessed, if available                                                                                       | Supplementary      |

|         |                                                                                    |             |
|---------|------------------------------------------------------------------------------------|-------------|
| Funding | 25 Sources of funding and other support (such as supply of drugs), role of funders | y file
4 |
|---------|------------------------------------------------------------------------------------|-------------|

\*We strongly recommend reading this statement in conjunction with the CONSORT 2010 Explanation and Elaboration for important clarifications on all the items. If relevant, we also recommend reading CONSORT extensions for cluster randomised trials, non-inferiority and equivalence trials, non-pharmacological treatments, herbal interventions, and pragmatic trials. Additional extensions are forthcoming: for those and for up to date references relevant to this checklist, see [www.consort-statement.org](http://www.consort-statement.org).

## Supplementary Data 3

### Telephone Interview

- 1. Could you tell me the name of the medical condition you have been diagnosed with and explain what it is in your own words?**

☐ Insufficient ☐ Sufficient ☐ Good ☐ Excellent

- 2. Have you been prescribed new take-home medications in the Emergency Department for this medical condition?**

☐ Insufficient ☐ Sufficient ☐ Good ☐ Excellent

- 3a). (For those patients who have been prescribed new take-home medications) What are these drugs for and for how long should you take them? What are the possible complications of your medical condition?**

☐ Insufficient ☐ Sufficient ☐ Good ☐ Excellent

- 3b). (For patients who have not been prescribed new take-home medications) Do you know why you have not been prescribed new medications? When are you going to have a follow-up visit? What are the possible complications of your medical condition?**

☐ Insufficient ☐ Sufficient ☐ Good ☐ Excellent

- 4. What symptoms would worry you enough to return to the Emergency Department?**

☐ Insufficient ☐ Sufficient ☐ Good ☐ Excellent

- 5. While in the Emergency Department did you get a chance to ask your doctor questions on your medical condition?**

☐ No, none of them ☐ Only a few of them ☐ Nearly all I had in mind ☐ Yes, all of them

**6. How would you assess the overall clarity of communication in the Emergency Department?**

☐ Insufficient ☐ Sufficient ☐ Good ☐ Excellent

**Patient's Level of Education (Years of Education):** ☐ <5 ☐ 5-8 ☐ 8-13 ☐ >13

## Supplementary Data 4

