## Objectives

The aim of this study is to assess the utility of two interventional videos, shown to patients discharged from the ED with a diagnosis of atrial fibrillation or deep vein thrombosis. We have focused our attention on these two medical conditions because they share some important features: they are frequently seen in EDs; their main complication (stroke and pulmonary embolism) can cause significant morbidity and mortality; both conditions and their related complications are probably not

very intuitive to comprehend for the general population. In fact, the understanding of these conditions implies the knowledge of a number of pathological processes, with which most people are unfamiliar.

The primary hypothesis is that patients enrolled in the study group will show a higher degree of comprehension of their medical condition and its related complications, as compared to the control group. Secondly, we will also analyze any possible effect of the videos on the knowledge of the therapy prescribed, return instructions and patients' satisfaction with the quality of communication in the ED.

Eventually, we will examine the association of some factors with the outcomes (age, sex, level of education, atrial fibrillation vs. deep vein thrombosis group).

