## Eligibility criteria

Inclusion criteria are the following:

- Age >18
- Being diagnosed with one of the two medical conditions under study: patients with first-time diagnosis of deep vein thrombosis; patients with first-time diagnosis of atrial fibrillation; patients with second episode in life of atrial fibrillation who have never been prescribed take-home medications for its cure or prevention of recurrence (anticoagulants, antiarrhythmic drugs including beta-blockers)
- Being discharged home directly from the Emergency Department/Emergency Unit
- Capacity of the patient to understand the explanations and instructions provided by the doctor (this includes excellent command of the Italian language)
- Having provided a valid phone number
- Having signed the informed consent

In case of patients lacking capacity, and in all cases of patients judged by the recruiting doctor as incapable to safely receive the discharge instructions, the caregiver will be enrolled to the study with identical modalities.

In the context of a pragmatic trial, we did not set exclusion criteria in terms of education level and comorbidities of the enrolled patients.

Exclusion criteria:

- Previous diagnosis of deep vein thrombosis
- Two or more previous episodes of atrial fibrillation; or one previous episode of atrial fibrillation for which the patient has been prescribed one of the following take-home medications: anticoagulants, antiarrhythmic drugs including beta-blockers.
- Being hospitalized

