## **Participants timeline**

Patient enrolment will take place in the emergency departments without any time restriction, including night shifts and festivities. Nevertheless, it is possible that the enrolment of eligible patients does not occur in a continuous fashion, as not all the doctors serving in the department participate in the study.

Prior to the discharge of eligible patients, the SIs will invite patients (or caregivers) to participate to the study, explaining its purpose and the methods used. Patients (or caregivers) willing to participate will sign the consent, provide a valid telephone number and are assigned to the study or control group. After patient's discharge, the SIs will transmit the telephone number to the PIs in charge of conducting interviews.

Telephone interviews will be carried out within 48 hours from discharge, using an institutional telephone station located in the emergency department of the IRCCS Fondazione Policlinico San Matteo Hospital.

The telephone station is connected to the institutional computer situated in the same room, which is provided with a free downloadable software for phone call management. All recordings will be stored on the same computer and each file is named with a progressive number code.

The equipment used to carry out phone interviews are situated in the same room where all files related to the study will be stored (consents, discharge letters, opaque envelopes for randomization).

Interviewers will try to contact patients (or caregivers) telephonically with a maximum of five attempts, after which the patients will be considered lost to follow-up.

During a patient's permanence within the emergency department, the SIs do not anticipate to the patient the content of the telephone interview, in order not to influence their answers.

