## **Sample size**

We hypothesize a median score for the primary outcome to be 10 points in the control group, whereas we expect a 20% higher score in the intervention group as suggested by current literature, with standard deviation 4 and non-normal distribution. Group sample sizes of 64 and 64 achieve 80% power to detect this difference with alpha error 5% using a two-sided Mann-Whitney test assuming that the actual distribution is uniform. (Note: this number represents the total number of patients with either DVT or AF, within each study group, since we do not expect differences in the effect by diagnosis).

Since we expect the number of patients lost to follow-up to be 10%, we plan to enroll 72 patients in each group (144 patients in total).

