### **Statistical analyses**

Descriptive statistics will be obtained for all variables assessed in the study population. Mean and standard deviation will be used for normally distributed variables, mean and interquartile range for skewed distributions, proportions for categorical variables. Whenever relevant, 95% confidence intervals (95% CI) will be calculated.

Groups will be compared by means of parametric or nonparametric tests for quantitative variables (according to distribution; normality will be tested by means of the Shapiro–Wilk test) and Pearson’s  $\chi^2$  test (Fisher exact test where appropriate) for categorical variables. In all cases, two-tailed tests will be applied. P-value  $<0.05$  will be considered significant. Bonferroni correction will be used whenever relevant.

Factors potentially associated to knowledge and to patient’s satisfaction, including age, gender, comorbidities, years of education will be tested by means of univariate and multivariate quantile (median) regression models.

Stata computer software version 15 or higher (Stata Corporation, [name]) will be used for statistical analysis.

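### The interview form asks only for the patient's education and does not record who answered, so for caregiver respondents the education analysis can pair one person's knowledge with another person's schooling

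*Protocol*

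**What the plan says.** Under Eligibility criteria, when the patient lacks capacity or the enrolling doctor thinks the instructions cannot safely be given to the patient, "the caregiver will be enrolled to the study with identical modalities". Participants timeline carries this through to the outcome: "Interviewers will try to contact patients (or caregivers) telephonically with a maximum of five attempts". In these cases the person who hears the explanation, takes the call and is scored is the caregiver.

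The instrument in Supplementary Data 3 is worded for a patient throughout. Question 1 begins "Could you tell me the name of the medical condition you have been diagnosed with". After question 6 comes a single four-band education item, labelled as the patient's: "Level of Education (Years of Education". The printed form has no field for who answered and no second education item.

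Education is then used as an explanatory variable. Objectives says "we will examine the association of some factors with the outcomes (age, sex, level of education, atrial fibrillation vs. deep vein thrombosis group". Statistical analyses names the factors and the method: "including age, gender, comorbidities, years of education will be tested by means of univariate and multivariate quantile (median) regression models".

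**The concern.** A comprehension score measures the person who answers. An association between schooling and comprehension means something only if both belong to the same person. If the form is completed as labelled, each caregiver respondent adds a record in which they do not.

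At stake is the education association with knowledge and with satisfaction, which is a stated objective. The mismatch pulls the estimate towards zero, so a real education gradient could be under-reported or missed. Because the printed form has no respondent field, an analyst working from it could neither detect nor correct this.

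**Working it through.** **What is and is not touched.** The only stated figure nearby is the sample size. Sample size gives "We hypothesize a median score for the primary outcome to be 10 points in the control group", a 20% higher score with the video (difference 2) and SD 4. The usual formula gives 2 × (1.96 + 0.84)² × (4/2)² = 62.8, so 63 per group, close to the stated 64. Then 64/0.90 = 71.1, so 72 per group and 144 in total, as stated. Education does not enter this calculation, and it does not enter the two-sample comparison of arms.

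**Size of the dilution.** Let P be the patient's education (recorded), C the caregiver's, c the share of caregiver respondents, r the correlation of P and C, and b the true slope. Patient respondents score a + bP and caregivers a + bC. Assume equal means and variances of P and C, and that having a caregiver respondent is unrelated to P. Regressing the score on P then gives a slope of b × [(1−c) + c·r].

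Neither c nor r is in the protocol, so the values below are assumptions.

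| c | caregivers among 144 | r = 0 | r = 0.3 | r = 0.5 |
|---|---|---|---|---|
| 5% | 7 | 0.95 | 0.965 | 0.975 |
| 10% | 14 | 0.90 | 0.93 | 0.95 |
| 20% | 29 | 0.80 | 0.86 | 0.90 |
| 30% | 43 | 0.70 | 0.79 | 0.85 |

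**Does it carry over to median regression?** The formula is a mean-regression result, while the plan uses median regression on banded education. A simulation checks this: 144 participants, four equally likely bands, true slope 1 point per band, residual SD 3.8, 600 replicates per setting. All of these settings are assumptions. Simulation error is about 0.015 for the slope and 0.02 for power.

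| c | slope, r = 0 | power, r = 0 | slope, r = 0.3 | power, r = 0.3 |
|---|---|---|---|---|
| 0% | 1.003 | 0.757 | 0.997 | 0.750 |
| 5% | 0.960 | 0.713 | 0.967 | 0.720 |
| 10% | 0.904 | 0.642 | 0.948 | 0.725 |
| 20% | 0.823 | 0.568 | 0.874 | 0.635 |
| 30% | 0.717 | 0.447 | 0.807 | 0.545 |

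The formula holds well enough for median regression.

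**Against sampling error.** Power of 0.757 for a slope of 1 implies a standard error of about 1/(1.96 + 0.70) = 0.38. At c = 10% and r = 0 the shift of 0.10 is 0.10/0.38, about a quarter of a standard error. At c = 20% the shift of 0.20 is about half of one.

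**The case against.** The strongest reply is that the label is loose. The interview and the scoring guide (Supplementary Data 4) say patient for whoever answers, and question 1 fits a caregiver no better than the education item does. Since caregivers are enrolled on identical terms, the education line could be read consistently as the respondent's. This has force: the protocol does not prove that the wrong person's education was entered. But Participants timeline, the follow-up text in Outcomes, and Ethics and dissemination all name patients and caregivers separately, so the label cannot be assumed to cover both. Even on the loose reading, the form does not show whose education was written down.

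A second reply is that the eCRF, the data management plan and the analysis plan are not shown, and that age, sex and comorbidities must be collected somewhere other than this sheet. That stands for age and sex. A reader might infer that the patient's age and sex are also attached to caregiver scores and that the age association is therefore biased. The protocol does not say whose age and sex are used, and the direction of any such bias would be a further assumption. The reply is weaker for education, because the printed form itself fixes whose education is asked for, and a later choice of model cannot supply a value that was never collected.

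A third reply is that the effect may be small. Patient capacity is an inclusion criterion and caregivers are the alternative route, so c may be low. At 5 to 10% the dilution is well inside sampling error. This also stands.

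**Conclusion.** The point holds as a minor defect in data capture. It is firm for education and for the missing respondent field on the printed form. It concerns only the factor analysis, which Objectives lists last. Its size depends on two quantities the protocol does not give. With r from 0 to 0.5, the education slope would be 0.90 to 0.95 of its true value if 10% of respondents were caregivers and 0.80 to 0.90 if 20% were, assuming the form was filled in as labelled and patients and caregivers have similar education distributions.

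A reader might go further and infer that the video-versus-control comparison is biased, or that a covariate-adjusted arm effect loses precision. The document supports neither. Randomisation protects the arm comparison whoever answers, and Statistical analyses compares the arms with two-sample tests and specifies no covariate-adjusted comparison of them.

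**What to change.** - Label the education item as the respondent's, and add a field stating whether the patient or a caregiver answered.
- Use the respondent's own education in the factor models, and likewise the respondent's age and sex if these are otherwise taken from the patient. Diagnosis and comorbidities stay the patient's.
- Add respondent type as a covariate, or repeat the factor analysis in patient respondents only.

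Supplementary Data 5 already reports 137 interviewed participants out of 144, so new form fields cannot help those records. For them, identify the respondent from the consent signed by the patient or caregiver, or from the audio recording. Outcomes already plans a further listen to the recordings for anticoagulant adherence, and respondent type could be noted in the same pass. Then report the number of caregiver respondents and the patient-respondents-only analysis.

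The cost is a few form fields and one model term or one sensitivity analysis. The patient-only analysis loses the caregiver records and so some precision. The randomised analysis and the sample size do not change.
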